### Interim analyses {21b}

No formal interim analysis is planned due to the small sample size and short treatment duration. The study is not designed for early stopping based on efficacy or futility. Adverse events will be monitored continuously throughout the trial by the study investigators.

### Plans to give access to the full protocol, participant-level data, and statistical code {31c}

Data collected in this study will not be publicly accessible but could be made available upon request for academic purposes after de-identification.

### Oversight and monitoring {5d, 21a, 23}

The core members of this trial committee, including clinical trial experts, statisticians, and ethical advisors from the National Taiwan University Hospital Clinical Trial Center (NTUH-CTC), will provide advisory support for developing the trial protocol, monitoring data, supervising safety, and reporting adverse events. Periodic research audits will be carried out to ensure the trial’s adherence to the predetermined protocol and active progression. Ethical considerations and modifications to the study protocols will be overseen by the National Taiwan University Hospital Research Ethics Committee.

### Adverse event reporting and harms {22}

All adverse events (AEs) and serious adverse events (SAEs) will be monitored and recorded throughout the study period. Known potential adverse reactions to hydroxychloroquine, including rash, gastrointestinal upset, headache, and visual symptoms, will be specifically inquired about at each ophthalmologic and clinical follow-up visit. Unexpected adverse events will also be collected and documented. All reported events will be coded using the Medical Dictionary for Regulatory Activities (MedDRA) terminology where applicable. Both expected and unexpected adverse events will be included in the trial publications, following the Consolidated Standards of Reporting Trials (CONSORT) extension for harms reporting guidelines.

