## Methods: participants, interventions, and outcomes

### Study setting {9}

Patients with mild GO who have already achieved euthyroidism will be screened at Taipei, Bei-Hu, Cancer Center, and Hsin-Chu branches of National Taiwan University Hospital (NCT05126147). Participants will be enrolled and randomly assigned in a 2:1 ratio to treatment or control group. The treatment group will receive HCQ 200 mg twice daily for a duration of 6 months, followed by a 6-month observation period, while the control group will receive standard of care for GO by endocrinologists. Participants will be enrolled by endocrinologists after screening of the inclusion and exclusion criteria. Ophthalmic measurements will be performed by the same ophthalmologist specializing in GO in each hospital to avoid inter-observer differences. In addition, ophthalmologists will be blinded to the participants’ treatment groups. They will be excluded from any role in allocation or treatment decisions and conducted evaluations according to standardized procedures.

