### Assignment of interventions: blinding {17a, 17b}

This study is an open-label study, so all participants and treating physicians will be unblinded. To minimize detection bias, ophthalmologists performing outcome assessments will be blinded to group allocation. They have no role in randomization or participant assignment and will perform standardized evaluations without access to treatment status.

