### Data collection and management {18a, 19}

Study nurses will make appointments with patients to ensure essential data are collected completely, including baseline information, lab data, GO-QoL, orbital CT, and ophthalmic examinations according to study schedule (Table 2). All clinical data will be recorded in standardized case report forms (CRFs) by trained study nurses at each study site. After data collection, information will be stored electronically in either the electronic medical record system or the REDCap platform, a centralized, password-protected database accessible only through the internal hospital network to ensure privacy and confidentiality. All data entries will be validated through regular data audits, range checks, and periodic double-entry verification for critical variables. Access to the database will be restricted to authorized personnel only. Data will be anonymized using participant identification codes. The database is hosted on a secure institutional server with regular backups and encryption protocols to ensure data integrity and confidentiality. Detailed data collection in this study is shown as below:

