Basic information: At the time of enrollment, we will collect participants’ age, gender, nationality, smoking status or exposure to secondhand smoke, types of thyroid disease, treatments received for thyroid disease in the past, current medications, duration of eye symptoms, and autoimmune diseases. Additionally, it is necessary to inquire if the patient is pregnant or planning to become pregnant, and a urine pregnancy test may be conducted if needed to rule out the possibility of pregnancy.GO-QoL will be obtained at enrollment and at the 12th, 24th, and 48th weeks. This internationally recognized questionnaire, validated for both quantification and validity, will be administered by study nurses [13]. It is designed to assess the quality of life in patients with GO, focusing on two main aspects: visual functioning and appearance subscales. Scores for each aspect are calculated separately, with a maximum score of 100 points each; lower scores indicate a greater impact on quality of life. This questionnaire has been translated into traditional Chinese and used in prior research and published internationally [17].Ophthalmological examinations will be conducted by the same ophthalmologist in each hospital. Three main metrics will be measured: eyelid aperture, soft tissue involvement, and exophthalmos using a Hertel exophthalmometer. These metrics are the primary outcomes of the study. Other assessments, including diplopia evaluated using the Gorman score [15], clinical activity score, and visual acuity, will also be recorded in detail. Given the potential side effect of hydroxychloroquine causing retinopathy [18], ophthalmologists will perform baseline and follow-up retinal toxicity assessments, including optical coherence tomography (OCT) and automated visual field testing when indicated.Orbital non-contrast CT will be conducted to evaluate changes in CT measurement values before enrollment, after medication, and after discontinuation of medication. Measurements for orbital volumetry will be based on a unified method adopted in numerous studies [14]. Parameters will include muscle volume (MV), fat volume (FV), orbital volume (OV), MV/OV ratio, FV/OV ratio, exophthalmos length (distance from interzygomatic line to the apex of the cornea), mean density of muscle, and mean density of fat.

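### Assessor blinding is not assured: the ophthalmologists who grade the primary outcome also appear to do the HCQ retinal-toxicity checks, and HCQ side effects are asked about at their visits

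*Protocol article*

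**What the plan says.** **On blinding.** Under Study setting {9}, "ophthalmologists will be blinded to the participants’ treatment groups", and they have no part in allocation or treatment decisions. Under blinding {17a, 17b}, "all participants and treating physicians will be unblinded", but "ophthalmologists performing outcome assessments will be blinded to group allocation", and these assessors "will perform standardized evaluations without access to treatment status". The Discussion names this blinding among its answers to detection bias.

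**On who examines.** Data collection and management {18a, 19} states: "Ophthalmological examinations will be conducted by the same ophthalmologist in each hospital". The examination covers lid aperture, soft tissue and Hertel readings, which make up the primary outcome.

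**On safety work.** The same item of {18a, 19} continues, giving HCQ retinopathy as the reason, that "ophthalmologists will perform baseline and follow-up retinal toxicity assessments, including optical coherence tomography (OCT) and automated visual field testing when indicated". Adverse event reporting and harms {22} says that known HCQ reactions, visual symptoms among them, "will be specifically inquired about at each ophthalmologic and clinical follow-up visit".

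**On the endpoint.** In Table 1, a fall of one grade in NOSPECS class 2 signs is enough for improvement, provided that no deterioration criterion is met.

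**The concern.** The article asks the same ophthalmologists to work without knowing the arm and, on its most natural reading, to look for toxicity of the one drug that separates the arms. It also places questions about that drug's side effects at the ophthalmologic visit, where an arm-aware participant can easily disclose treatment in answering. One ophthalmologist examines throughout at each hospital, so what is learned at one visit can carry to the week 24 and week 48 gradings.

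Oedema, injection and chemosis are graded by clinical judgement, and lid aperture and Hertel readings also depend on the examiner. A small lean in soft-tissue grading is enough to turn a stable participant into an improver. If graders learn the arm and lean towards HCQ, part of an apparent treatment effect could come from the grading, and analysis cannot remove that afterwards.

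**Working it through.** **Step 1. Set the sections side by side.**

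| Question | What the article states | What it leaves open |
|---|---|---|
| Is the grader blinded? | Yes: {9}, {17a, 17b}, Discussion | How the grader is shielded |
| Who grades? | One ophthalmologist per hospital: {9}, {18a, 19} | – |
| Who does the retinal-toxicity checks? | Ophthalmologists, in the same item as the outcome examination: {18a, 19} | Whether this is the grader; whether both arms are checked alike; what triggers the conditional tests |
| Where are HCQ reactions asked about? | At each ophthalmologic and clinical visit: {22} | Who asks; whether both arms are asked alike |
| Do participants know their arm? | Yes: {17a, 17b} | Whether they are told not to disclose it |

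The blinding statement and the task assignments can both hold only if the open items are settled in the right direction. The article does not settle them.

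**Step 2. Reproduce the plan's own figure.** Inputs from Sample size {14}: 12% versus 37%, 2:1 allocation, two-sided α of 0.05, 80% power. Pooled rate = (0.12 + 2 × 0.37)/3 = 0.2867.

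n(control) = [1.96·√(1.5 × 0.2867 × 0.7133) + 0.8416·√(0.12 × 0.88 + 0.37 × 0.63/2)]² / 0.25² = (1.0855 + 0.3967)²/0.0625 = 35.1, rounded up to 36.

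This gives 36 + 72 = 108, as stated, with power 81.0%. The sample size is not in dispute. It supplies the base rate and arm sizes for Step 3.

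**Step 3. Illustrate what biased grading could do.** The over-call rate is an assumption; the document gives none. Suppose the drug has no effect, the base rate is b in both arms, and a fraction o of HCQ non-improvers is graded as improved. Then:

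- observed HCQ rate q = b + (1 − b)·o
- difference d = q − b
- pooled rate p̄ = (36b + 72q)/108
- SE₀ = √[p̄(1 − p̄)(1/36 + 1/72)]
- SE₁ = √[b(1 − b)/36 + q(1 − q)/72]
- chance of a significant result favouring HCQ = Φ[(d − 1.96·SE₀)/SE₁]

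Worked case, b = 0.12 and o = 0.10: q = 0.12 + 0.88 × 0.10 = 0.208; d = 0.088; p̄ = 0.1787; SE₀ = 0.0782; SE₁ = 0.0723; Φ[(0.088 − 0.1533)/0.0723] = Φ(−0.903) = 0.183.

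| Base rate | Over-call | Observed HCQ rate | False result favouring HCQ |
|---|---|---|---|
| 12% | 0 | 12.0% | 2.5% |
| 12% | 3% | 14.6% | 5% |
| 12% | 5% | 16.4% | 8% |
| 12% | 10% | 20.8% | 18% |
| 12% | 15% | 25.2% | 34% |
| 30% (assumed) | 10% | 37.0% | 10% |
| 30% (assumed) | 15% | 40.5% | 18% |

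Summing exact binomial probabilities for the same z-test at the 12% base rate gives 18% for the 10% case and 35% for the 15% case. Fisher's exact test, which Statistical methods also allows, gives about 15% for the 10% case at a 12% base rate and about 9% at 30%.

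The over-call rate is an average over the whole HCQ arm. If the grader learned the arm of only half the HCQ participants, a 10% over-call among those would count as 5% overall, which is the 8% row.

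**The case against.** The strongest reply is that nothing in the text forces the grader to learn the arm.

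- **Who asks.** The harms section is in the passive and names no asker. Under {11c}, study nurses ask participants to report adverse events; under {18a, 19}, they record the clinical data. They may already ask the HCQ questions.
- **Which arm.** Neither the retinal checks nor the questions are limited to the HCQ group. The ECG is expressly limited to the treatment group, so silence elsewhere may mean that both arms are treated alike. Pre-existing retinal disease is an exclusion for everyone, so a baseline check in all participants is plausible. The same check or question applied to both arms does not by itself reveal the arm.
- **What triggers testing.** The condition on OCT and field testing is undefined. It may mean symptoms or an abnormal finding rather than drug exposure.
- **What is not shown.** Table 2, where a per-arm schedule would be expected, is missing from the text at hand. The order of assessments is the kind of detail that an article leaves to the full protocol.

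All of this stands against a claim that blinding fails as written, and a reader should not infer that. It does not remove the tension. The article itself places HCQ toxicity work with ophthalmologists, in the item that describes the outcome examination, and puts drug-specific questions to arm-aware people at the ophthalmologic visit. Even identical questions invite disclosure.

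A reader might also infer a leak through data systems, because "information will be stored electronically in either the electronic medical record system or the REDCap platform" and REDCap carries the allocation. The documents do not support that: allocation goes to principal investigators, database access is limited to authorised personnel, and nothing says that graders see allocation or prescriptions.

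**Conclusion.** The concern holds as a conflict to be reconciled: assessor blinding is claimed, but the tasks assigned elsewhere put it at risk, and the article states no safeguard that assures it. The better anchor is the retinal-toxicity sentence in {18a, 19}; the harms section supports it, but alone shows only where the questions are asked. That grader and retinal examiner are the same person is the natural reading, not an express statement.

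The 8%, 18% and 34% figures are conditional on assumed over-calling, always in favour of HCQ, with a 12% base rate and no drug effect. They show how sensitive a trial of 72 versus 36 is to modest grading bias. They do not estimate the bias in this trial, and smaller or partial unblinding gives smaller figures.

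This should be fixed; confidence is moderate.

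**What to change.** Reconcile the blinding, data collection and harms sections so that they state the following:

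1. At every visit the ophthalmologist records and locks the lid aperture, NOSPECS and Hertel readings before any retinal test or safety discussion.
2. The study nurse or endocrinologist, not the grader, asks the HCQ adverse-reaction questions.
3. Participants are told not to reveal their arm to the ophthalmologist who grades them.
4. The grader's guess of the arm is recorded at week 24, so that the success of blinding can be reported.

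The text should also say who performs the retinal assessments and whether both arms receive them in the same way. When or in whom retinal testing is done is a clinical matter, and no change to it is proposed here.

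The cost is minor visit scheduling. Nurses and endocrinologists are already in contact with participants, so no new staff are needed.

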### Protocol amendments {25}

Any modifications to the protocol that may impact study conduct, participant safety, or study outcomes—including changes to eligibility criteria, outcomes, analyses, or study procedures—will be submitted to the Research Ethics Committee (REC) in National Taiwan University Hospital for review and approval prior to implementation. Substantial protocol amendments will also be updated in the ClinicalTrials.gov registration and communicated to investigators and participants as appropriate. All amendments will be reported in future trial publications.

## Discussion

There have been unmet medical needs for patients with mild GO, given that they still suffer from overt decline of quality of life [13, 19]. Despite the discovery in 2011 that selenium supplementation could benefit patients with mild GO, documented by a RCT published in the *New England Journal of Medicine* [4], there are no other effective medications emerged since then. In addition, the effect of selenium in selenium-sufficient region remains questionable to date [7]. Furthermore, the exploration of other potential treatments for mild GO has been limited, with few clinical trials registered or ongoing on ClinicalTrials.gov.

In 2020, one cell study published in the *Journal of Clinical Endocrinology and Metabolism* showed the effects of HCQ on orbital fibroblasts [2]. It disclosed new possibilities on this challenging disease, and this pivotal finding has motivated the initiation of our clinical trial to ascertain whether HCQ’s effects could be replicated in patients with mild GO.

In this open-label study, we acknowledge potential biases such as performance and detection bias. To mitigate these, we will ensure that all participants receive the same standard of care in accordance with EUGOGO guidelines. Ophthalmologists performing outcome assessments will be blinded to group allocation and will not be involved in participant randomization or treatment delivery. They will conduct standardized assessments independently to reduce subjective bias. Additionally, the study will utilize randomized participant selection and objective outcome measures such as ophthalmic outcome and orbital CT parameters to further reduce the risks of selection and reporting biases.

Several challenges may be encountered in the conduct of this clinical trial. For example, the randomization process makes some patients felt uncertain, especially in those who are eager to receive effective medications, which can be overcome through further explanation of the scientific rationale for randomization. In addition, concerns about the potential side effects of HCQ, such as retinopathy, have been raised in the literature. This has contributed to hesitancy in joining the study, particularly among patients with mild GO whose quality of life is only minimally affected. These questions will be addressed by providing detailed information about the likelihood of such effects and the monitoring strategies in place. Finally, potential operational challenges, such as scheduling or communication difficulties, have been anticipated and addressed through flexible coordination strategies, including proactive use of social messaging platforms, appointment reminders, and individualized rescheduling when necessary. 

In conclusion, this protocol outlines a randomized controlled trial designed to address the unmet therapeutic needs of patients with mild GO. By anticipating potential recruitment, operational, and compliance challenges, we have incorporated adaptive strategies and resource planning to support trial implementation. We expect that the results of this study will contribute to the development of novel treatment strategies for patients with mild GO. 

## Data Availability

Data collected in this study will not be publicly accessible but could be made available upon request for academic purposes after de-identification.

## Abbreviations

ALT: Alanine aminotransferase
ANOVA: Analysis of variance
AST: Aspartate aminotransferase
ATA: American Thyroid Association
anti-TPO: Anti-thyroid peroxidase antibodies
ATA: Anti-thyroglobulin antibody
CAS: Clinical activity score
CT: Computed tomography
DMC: Data monitoring committee
eGFR: Estimated glomerular filtration rate
ETA: European Thyroid Association
EUGOGO: European Group on Graves’ orbitopathy
free T4: Free thyroxine
FV: Fat volume
G6PD: Glucose-6-phosphate dehydrogenase
GAGs: Glycosaminoglycans
GD: Graves’ disease
GO: Graves’ orbitopathy
GO-QoL: GO-Quality of Life Questionnaire
HCQ: Hydroxychloroquine
IFN-γ: Interferon γ
IL-1β: Interleukin 1β
IL-6: Interleukin 6
MCID: Minimal clinically important difference
MV: Muscle volume
NTUH-SCU: National Taiwan University Hospital Statistical Consulting Unit
NTUH-CTC: National Taiwan University Hospital Clinical Trial Center
OV: Orbital volume
RCT: Randomized controlled trial
TBII: Thyrotropin-binding inhibitory immunoglobulins
TGF-β: Transforming growth factor β
TNF-α: Tumor necrosis factor α
TSH: Thyroid-stimulating hormone
